#### Level 2: Couple-Level Eligibility for Relationship Verification

Web-based relationship verification and validation techniques, which entails a series of questions that compares both the partners’ responses about their relationship (eg, partners’ birth month, tattoo, cohabitation, and pet ownership) will be used [25,26], Relationship verification is based on both partners’ responses to 7 screener items that are automatically evaluated against predetermined decision rules. The 7 items that will be used include age, birth month, relationship status, relationship length, cohabitation, owning pets, and having tattoos. Couples with both partners who provide answers that crossmatch to at least 5 of the 7 questions will be deemed as passing the relationship verification criteria. Couples who do not pass the relationship verification process will not be allowed to participate in the study even if they meet the eligibility criteria of level 1. The relationship verification process of level 2 is in place to help ensure that web-based data will be collected from participants who are in a relationship with one another. Couples who do not pass level 2 eligibility will be thanked for their interest in the study and provided a list of HIV and STI prevention care resources and other health and relationship-oriented resources available in Lima. Couples who meet level 2 eligibility criteria will be invited to attend a brief onboarding Zoom meeting with a staff member of the study.

#### Level 3: Study Onboarding Zoom Meeting

Couples who meet all eligible criteria, provide e-consent, enter complete and accurate contact information, and pass the requirements for *relationship verification and data validation* will be invited to partake in a 10 to 15-minute onboarding Zoom meeting. During the meeting, the study staff will assess the couples’ verification and interest in participating, discuss study expectations and timelines, answer questions, and decide whether to admit the couple into the study. Once admitted, each partner of the couple will be asked to create their own profile on the P3 DHI using their own web-connected device. Their profile will give them access to the baseline assessment followed by whichever intervention group they are randomly assigned to for the pilot RCT.

### Web-Based Fraud Deterrent and Data Validity Safeguards

A variety of fraud deterrents will be embedded and programmed into the eligibility screener to help deter the infiltration of “bots” and fraudulent data entries. Specifically, the eligibility screener will only allow entries from Peru-based IP addresses; no more than 3 screener entries may originate from the same IP address. Start and stop times of completed screener entries will also be monitored and evaluated against a predetermined minimum time for completion. Once an electronically screened individual is deemed eligible for level 1 criteria and has provided e-consent, they will be required to validate their WhatsApp number by entering a 4-digit code sent to their WhatsApp number and entering that specific code in the DHI web system.

Data validity safeguards will also be used to determine whether responses come from 2 unique individuals in a relationship and not from 1 person pretending to be 2 people (ie, fraudulent responses). The eligibility screener date and completion times of couples who pass levels 1 and 2 of the eligibility criteria will also be examined in conjunction with corresponding IP addresses for these entries. Back-to-back screener entries (ie, the start time of the new entry closely following the stop time of the previous entry) and entries specifically from the same IP address will be flagged for review by examining other eligibility criteria and contact information. Overall, each couple must pass the first 2 validation criteria and have no more than 3 screener entries between them. The investigative team uses these relationship verification and data validation test processes to identify true couples in previous and ongoing web-based studies involving couples.

### Ethical Considerations

The FIU and Universidad Peruana Cayetano Heredia Institutional Review Board approved all study-related activities for the 6-month pilot RCT of the P3 DHI (IRB-22-0496, IRB 201101). The project will have a certificate of confidentiality in place as a requirement of the funding agency. The e-consent form will inform participants of confidentiality guidelines and standards. No identifying data will be collected before informed consent is received from the participants; each partner will be required to individually provide consent electronically. The participants will be informed to complete the eligibility screener in a location they deem to be private. If a participant decides to withdraw from the study after providing consent and identifying data (eg, name, email address, and WhatsApp number), then any identifying data associated with the participant will be deleted. In addition, the participants will be instructed to participate in the individual, qualitative exit interview via Zoom or in person at Epicentro in a private setting or a room; the study staff will also be hosting these interviews in a private setting, either on a computer or using a digital recorder. Finally, all correspondence with the participants will be devoid of any indication of the content, purpose, or target population of the study; the participants will be encouraged to delete correspondence (eg, WhatsApp messages) as soon as the participant decides they no longer need the contained information.

Regarding confidentiality and data management practices, neither partner will have access to the other partner’s test results or data from assessments or interviews. Each study participant will be required to create and use a username and unique passcode to gain access and use the P3 DHI. Furthermore, the participants will be automatically logged out of the P3 DHI after a period of inactivity. All data will be coded by a unique individual study number, and personal identifier records will be kept in password-protected files on password-protected computers. HIV and STI test results will be coded using the participant ID; this ID will not have any potential identifying information and will only be accessible to study staff. All recorded videos on Zoom will only occur on the study staff’s secure laptop (password protected and in password-protected files). Similarly, all recorded audio files will only be available on the study staff’s designated digital recorder. From this recorder, the audio will then be immediately uploaded to the study staff’s secure laptop (password protected files). Records will be kept confidential to the level allowed by law, and only the staff assigned to the study will have access to nonanonymous records. Information provided by the study participants will not be released to outside sources unless legally required or written consent is provided by the study participant.

All eligibility screener, consent, and intervention use (ie, paradata) data will be collected and blockchain encrypted via the P3 DHI secure web app hosted on a secure server (Azure; Microsoft Corp). Quantitative baseline and follow-up assessment data will be collected and managed using Qualtrics, an electronic survey data-capturing tool at FIU. Qualtrics is a secure, web-based survey application that is compliant with the Health Insurance Portability and Accountability Act. All Qualtrics servers are backed up daily and monitored for hardware failures. At the end of the trial, all data for the study will be stored on OneDrive, which will only be accessible to the study team through an SSL-encrypted connection that backs FIU’s firewall system.

### Randomization

An allocated randomization block of 2:2, via an embedded algorithm within the P3 DHI, will be used to randomly assign couples to one of the following 2 intervention conditions following the baseline assessment: (1) an immediate intervention condition where couples will be able to use the P3 DHI for 6 months or (2) a 3-month delayed intervention condition where couples will be able to use the P3 DHI for the last 3 months of the trial. For ethical reasons, a delayed control condition was chosen for the trial study to provide all couples with access to the intervention while also permitting the ability to compare outcome differences between trial arms for the first 3 months of the pilot RCT. In sum, all couples in the pilot RCT will have access to use the P3 DHI for a minimum of 3 months, which will enable data pooling of the entire couple sample (N=60; ie, first 3 months for the immediate intervention condition plus the last 3 months with the delayed intervention condition). The study design will also enable the examination of long-term effects of the P3 DHI (ie, effects after 6 months of use) on outcomes and their use of the P3 DHI among couples randomized to the immediate intervention condition (n=30). Randomization will be blinded to couples but not to the study staff (administrators).

### Pilot RCT Baseline and Follow-Up Measures

Items about evaluation will only be assessed during follow-ups after the participants receive the intervention. All other measures, items, and scales will be assessed at each time point throughout the trial, including baseline. In addition to screening for inclusion, the eligibility screener will capture a variety of demographic information from each participant including age, race, sex at birth, gender identity, sexual identity, highest education attainment, current employment status, has a primary health care provider, relationship type, relationship length, couple cohabitation, and couple HIV serostatus. Other demographic information will be captured at each data collection time point (ie, at baseline, months 3 and 6) to assess participant’s current living arrangement, type of health insurance, affordability to pay for health care or medication costs when needed in the past 3 months, as well as whether participants were in a situation that required them to reduce a meal size or skip a meal because of not having enough money for food in the past 3 months (social determinants of health). Skip patterns will be used accordingly for baseline and follow-up assessments at months 3 and 6. Multimedia Appendix 1 [24,27-49] provides a brief description of all other items and scales that will be assessed at each time point and how they relate to the constructs of CIT-HBC [13,14].

Beyond the General Anxiety Disorder 2-item, 5 other items will be used to capture aspects about anxiety and worry specifically related to sex and being in a relationship. The items include the following: “Do you ever feel like you are walking on eggshells around your partner? (Yes, No, I don’t remember)”; “In thinking about the past 3 months, how much did you worry or feel anxious about having sex with your partner? (0=never to 4=always)”; “To what extent did this anxiety stop you from enjoying sex with your partner? (0=not at all to 2=a lot)”; “In thinking about the past 3 months, how much did you worry or feel anxious about having sex with others, not including your partner? (0=never to 4=always)”; and “To what extent did this anxiety stop you from enjoying sex with others, not including your partner? (0=not at all to 2=a lot).” Skip patterns will be used for the above set of items such that some items may not be displayed depending on the participant’s response to the previous item.

Furthermore, some scales will be modified based on feedback from the Community Advisory Board and to help reduce time burden for participants. For instance, single global items from validated scales (eg, Dyadic Trust Scale [34] and Investment Model short form [36]) may alternatively be used to capture interpersonal trust, relationship commitment, and relationship satisfaction instead of the complete scale.

In addition to self-reports of partners using strategies over time, we will ask each participant to test for HIV and STIs at baseline and at 6 months post baseline by going to a local community-based organization. Biological data for new diagnoses of HIV, chlamydia, gonorrhea, and syphilis will be collected. For those previously diagnosed with syphilis, the rapid plasma reagin test will be processed to examine antibodies to syphilis. HIV will be assessed using a rapid test, with a rapid test from another manufacturer used as a confirmatory test if the first is positive. GeneXpert polymerase chain reaction testing will be used to diagnose chlamydia and gonorrhea infections.

### Relationship Dissolution

It is possible that some couples may end their relationship during the eligibility and enrollment process (before enrollment) or sometimes after trial enrollment (eg, between 3 and 6 months after baseline). Couples who self-report that their relationship had ended (through a follow-up assessment or by contacting the study team directly) while participating in the 6-month pilot RCT will not be permitted to continue participating in the study as a couple or as a participant. Couples who end their relationship between assessments will be asked to complete one more assessment, capturing information on any influence they perceive the study to have had on the end of their relationship before being administratively removed from the trial. In an assessment, couples who self-report that their relationship had ended will be administratively removed from the trial afterward. To prevent contamination of the intervention, neither partner of couples who have broken up will be permitted to rejoin the study if or when they enter a new relationship, even if all eligibility criteria are met. We will check this by cross-checking the contact details of all partners in our contact database to ensure that prior participants are not reenrolled.

### Incentives

Each participant will receive an incentive (ie, cash) for their time associated with the study activities at set time points during the pilot trial: baseline 50 Peruvian Soles (US $14) for baseline and 55 Peruvian soles (US $15) for month 3 and month 6, respectively.

### Analytic Plan

#### Overview

For aim 1, we will define and measure feasibility as the ability to recruit, screen for eligibility, enroll, and retain couples in the 6-month pilot RCT over time. Our preliminary work [9-11] demonstrated our ability to recruit, screen for eligibility, and enroll eligible adult cisgender SMM couples in Lima, Peru. We will extend this work for the proposed project to assess feasibility with a larger sample of couples with a focus on retention for the 6-month pilot RCT. As such, some examples of the research questions we seek to answer through this specific aim are as follows: (1) Is it feasible to retain >90% of the couples in the 6-month pilot RCT? (2) Is it feasible to retain >90% of the couples who have both partners complete all 3 quantitative assessments (baseline, month 3, and month 6)? and (3) Is it feasible to have >90% of couples with both partners completing their individual-level, exit interview at 6 months? In line with common research practices (which can help inform a larger RCT), we will evaluate which recruitment strategies (eg, targeted advertisements placed on Facebook or Instagram vs in-person recruitment by research staff) led to the highest proportion of interested individuals starting or completing the eligibility screener as well as couple eligibility and consent. Through our established protocols (ie, standard operating procedures), the study will track and quantitatively describe the reasons why individuals and couples were ineligible, track enrollment rates among consented and eligible couples, assess retention among enrolled couples during the pilot RCT by arm, and which retention practices appealed to participants. The research will also track the reasons for attrition. A detailed CONSORT (Consolidated Standards of Reporting Trials) diagram will be produced at the conclusion of the pilot RCT. We will also quantitatively calculate the proportions of how many participants provided permission and documentation (paper or through the web portal) about their use of prevention strategies during the pilot RCT. We will apply the data obtained from the eligibility screeners to use descriptive statistics at the individual and couple levels and explore whether differences exist based on the couples’ HIV serostatus.

For aim 2, acceptability of P3 will be defined through participant and couples’ use of it (ie, paradata) as well as their attitudes from their experiences of using it over time (ie, quantitative and qualitative dyadic data). For each couple, the research will measure acceptability using and analyzing 3 types of data from both of the relationship partners: (1) quantitative measures will include the Health Information Technology Usability Evaluation scale [24], perceived effect of using P3 on a couples’ relationship [49], and self-reports of the number of intervention modules completed; (2) a qualitative, individual exit interview will be conducted to provide context and supplement partners’ responses to their quantitative measures as well as their top 3 likes, top 3 dislikes, and recommendations to enhance P3; and (3) paradata from the couples’ use of the intervention over time (eg, module completion and time to complete each module).

#### Quantitative Measures

All statistical analyses will be performed with SAS (SAS Institute) or Stata (version 14.2; StataCorp) with modeling using PROC MIXED or GLIMIMIX. We will generate descriptive statistics to calculate means, SDs, counts, and proportions at the individual and couple levels for the Health Information Technology Usability Evaluation scale [24] (mean and SD) and other evaluation items and by dyad HIV serostatus group. The study will also explore, univariately, whether differences exist by couples’ HIV serostatus for these quantitative measures by applying ANOVA and chi-square tests for couple-level continuous and categorical independent variables, respectively.

#### Qualitative Measures

The study will conduct content analysis [50,51] of the qualitative dyadic data collected through the exit interviews at the final follow-up in the pilot trial. Specifically, we will conduct summative content analysis [50,51] of P3 to generate counts and proportions of how many couples had one or both partners mention keywords, topics, or activities, by trial arm, and by couple HIV status. We will also conduct conventional content analysis [50,51] of the qualitative dyadic data to generate coding categories from the transcripts, which may illuminate broader themes of what participants or couples liked and used in P3. Emergent themes may include the use of infographics in educational content about different topics covered, answering questions in the activities to receive tailored recommendations, or watching videos. At least 3 research team members will read all transcripts, take notes, and identify overarching themes. The team will then meet to discuss the overarching themes before rereading and coding the transcripts for these themes, starting with summative content analysis [50,51] to generate counts of keywords before repeating the process for conventional content analysis [50,51]. During subsequent meetings, the team will compare and discuss their coding and will make adjustments as needed before creating the codebook. The codebook will describe the themes and their corresponding definitions. Each team member will then use the codebook to code the transcripts once again. This process will be applied for all transcripts; then, each team member will review one another’s coding of the transcripts to ensure that consistency will be achieved for the themes identified (ie, interrater reliability >0.90). All coding will be done using a web-based management tool, such as Dedoose (9.2.012 Mac; Sociocultural Research Consultants LLC). In the end, a sum count of each individual-level response per theme will be calculated to describe the proportion of endorsement within and between couples for the entire sample, by arm, and by couple HIV serostatus resulting in tables to visualize these endorsements. Representative quotes will also be identified for use to disseminate findings in peer-reviewed outlets (eg, manuscripts and conferences).

#### Paradata From Use of the P3 Intervention

This research will generate descriptive statistics to calculate means, SDs, counts (with ranges), and proportions at the individual and couple levels from the dyadic paradata collected. Firstly, this study will calculate the number of couples who completed all 5 modules in the intervention (vs 4, 3, 2, 1, and none). The researchers will also calculate how much time the participants and couples took to complete each module (eg, module 1=10 minutes) and the total time taken to complete all 5 modules. Next, we will descriptively analyze couples’ responses to the various questions and activities embedded within each of the modules. For all the abovementioned analyses, we will explore whether differences exist by trial arm (eg, n=30 who immediately received the intervention vs n=30 in the delayed control group) and by couples’ HIV serostatus using comparative analyses.

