**Figure 2 figure2:**
[figure not shown]
Para Ti, Para Mí, Para Nosotros (P3) web app landing page to access the eligibility screener and the intervention via an “iniciar session.”.

In addition to a secure SMS text messaging system to communicate with participants, the P3 DHI also contains an administrative and clinical portal for researchers and staff. The administrative portal serves as a one-stop shop to store, organize, and monitor data associated with the trial. Along with its other features, the portal contains a dashboard and participant tracking system. The dashboard provides a global overview of all study participants and couples’ engagement with the study, ranging from data associated with eligibility and enrollment rates and information on assessment and module completions. The dashboard also offers researchers and staff the ability to download data about participants’ and couples’ experiences with regard to using the intervention modules within the P3 DHI. Finally, as each couple progresses through the trial, the participant tracking system provides descriptive details including due and completion dates of assessments as well as when and which modules are completed.

Both the dashboard and participant tracking system are interactive such that all numbers displayed in the dashboard provide the administrative user the ability to learn more about which specific participants or couples are linked to a particular characteristic in the dashboard (eg, number of enrolled couples in the immediate intervention arm). In addition, each participant and couple are assigned a unique ID. Selecting and clicking on the unique ID in the administrative portal leads to a web page providing information about the couple, their assessments (eg, due date and completion date), their module use (date of completion relative to assessment timeline for trial), links to their screener responses, when and which SMS text message reminders they have received, contact information, and HIV and STI testing details, including results. Figures 3 and 4 provide screenshot examples of the administrative portal.

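### Module completion is compared by arm without a common window, although one arm has 6 months of access and the other 3, so the comparison is confounded with length of access

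*Protocol article*

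**What the plan says.** The Randomization section of the protocol article defines "an immediate intervention condition where couples will be able to use the P3 DHI for 6 months" and "a 3-month delayed intervention condition where couples will be able to use the P3 DHI for the last 3 months of the trial".

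The section on paradata (aim 2, acceptability) lists three things to be derived from use of the intervention:

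- Completion: "this study will calculate the number of couples who completed all 5 modules in the intervention (vs 4, 3, 2, 1, and none").
- Time: "how much time the participants and couples took to complete each module (eg, module 1=10 minutes) and the total time taken to complete all 5".
- Responses: "we will descriptively analyze couples’ responses to the various questions and activities embedded within each of the modules".

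It closes with "For all the abovementioned analyses, we will explore whether differences exist by trial arm", naming 30 couples in each group, and also by couples' HIV serostatus. It gives no observation window and no adjustment for length of access, and it names no test for the comparison by arm.

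Elsewhere the article does match the windows. In Randomization, and again under Aim 3 (Preliminary Efficacy), the immediate arm's first 3 months are put together with the delayed arm's last 3 months for pooling. Randomization also treats use over 6 months as a question within the immediate arm. The paradata section does not carry the 3-month window over.

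**The concern.** The number of modules a couple has completed is cumulative: it cannot fall, and it can rise for as long as access lasts. One arm has twice as long to finish. A couple in the immediate arm that completes module 5 in month 5 counts as a full completer. A delayed-arm couple working at the same pace has no month 5 of access, and counts as incomplete. The two arms can therefore differ in completion even when couples in both take up P3 in exactly the same way.

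Paradata are one of three data sources for acceptability, and the pilot is meant to shape the next version of P3 and a larger trial. Higher completion in the immediate arm could be taken to mean that waiting dampens engagement, when it may reflect only the longer access.

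**Working it through.** **Inputs from the protocol article**

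- Access, immediate arm: 6 months (Randomization).
- Access, delayed arm: 3 months (Randomization). Ratio 6:3 = 2:1.
- Couples per arm: 30 planned (paradata section). Enrolment was 74 couples (Results), which is 37 per arm if split equally.
- α = .05 (Power, Sample Size, and Effect Size Estimations).
- Completion rate at 3 months: not given. A range is assumed below.

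The article states no expected completion rate or power for this comparison, so there is no figure of its own to reproduce.

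**Which of the three measures depend on access time**

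- Completion count: directly, because it accumulates.
- Time: no direct dependence. The article's example is 10 minutes for module 1, so this is the time a module takes, not the time since access opened. Access can matter only indirectly, through which couples get as far as finishing.
- Responses to activities: not a count of exposure. Any effect is again only through who reaches the activity.

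The point therefore concerns completion.

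**Case 1: equal and constant completion rate in both arms (assumption)**

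If a proportion p of couples has finished by 3 months, and those who have not finished do so at the same rate in the next 3 months, the proportion finished by 6 months is q = 1 − (1 − p)². The gap q − p arises with no true difference between arms. The last two columns give the exact rejection probability of an uncorrected two-sided chi-square test at .05, summed over the two binomial distributions.

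| p (3 months, delayed) | q (6 months, immediate) | Gap, points | Rejection, 30 per arm | Rejection, 37 per arm |
|---|---|---|---|---|
| 30% | 1 − 0.70² = 51% | 21 | 38% | 44% |
| 50% | 1 − 0.50² = 75% | 25 | 52% | 60% |
| 70% | 1 − 0.30² = 91% | 21 | 55% | 65% |
| 80% | 1 − 0.20² = 96% | 16 | 53% | 62% |

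**Case 2: most couples finish early (assumption)**

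Take 70% finished by month 3 in both arms, with a few more finishing in the immediate arm's second 3 months. At 30 per arm:

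| Finishing after month 3 | Immediate vs delayed | Rejection |
|---|---|---|
| 10 points | 80% vs 70% | 14% |
| 5 points | 75% vs 70% | 7% |
| 0 points | 70% vs 70% | 5% |

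**Check of the remedy**

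If both arms are cut at 3 months after access, equal uptake gives p in each arm, an expected gap of 0 and rejection at about the nominal 5%.

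**Can the data support the remedy?**

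The section on the user interface says that the administrative portal holds, for each couple, "their module use (date of completion relative to assessment timeline for trial"). Completion can therefore be counted up to any date, including 3 months after access.

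**The case against.** The strongest reply is that this is an exploratory comparison within one of three acceptability sources, and that the window for such a table is a detail a condensed article may leave to the full protocol or analysis plan. The authors clearly know that exposure differs, since they match windows for pooling and place 6-month use within the immediate arm. The design also favours early completion: five modules of 15 to 20 minutes each, with automated prompts to start and to finish. If nearly everyone finishes within 3 months, the artefact is close to nil.

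Much of this stands. It limits the size, and it means that the rejection rates are illustrations under a test the article does not name for this purpose. It does not remove the point. The article commits in print to comparing completion by arm and names the groups, and followed as written that comparison has unequal windows. Nothing in the article shows that completion is over by month 3. Both partners must finish each module before the next opens, which can slow a couple down.

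A reader might infer more than the article supports:

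- **That reuse is also compared by arm.** Reuse appears only in the Specific Aims, as a descriptive pattern of use.
- **That time is distorted in the same way.** It is the time a module takes, which does not grow with access.
- **That usability and evaluation scores are compared after unequal exposure.** The Quantitative Measures section compares these by HIV serostatus and states no comparison by arm. Their timing in the immediate arm is also not settled: one section says "Items about evaluation will only be assessed during follow-ups after the participants receive the intervention", while the Specific Aims place the usability scale at the final follow-up.
- **That the comparison measures nothing but exposure time.** It mixes access time with any real arm difference, in proportions the article does not let us determine.

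**Conclusion.** The point holds for module completion only. As written, the exploratory comparison by arm is confounded with a 2:1 difference in length of access. The spurious gap is 16 to 25 points if completion proceeds at an equal, constant rate and 30% to 80% of couples finish within 3 months. It shrinks to 10, 5 or 0 points if 70% finish by month 3 and few or none finish later. The completion rates, their pattern over time and the use of a chi-square test are all assumptions. The direction is not: with equal uptake, longer access can only favour the immediate arm.

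The consequence is limited to how acceptability is read. The efficacy outcomes A to D, the sample size and the retention targets do not depend on it.

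**What to change.** Add one sentence to the paradata section. For the comparison of module completion by arm, count only activity in the first 3 months after access in each arm: baseline to month 3 for the immediate arm, month 3 to month 6 for the delayed arm. Apply the same window to reuse if it is compared by arm. Report the immediate arm's months 3 to 6 separately, as sustained use.

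The cost is that sentence and a date cut-off in the analysis. Completion dates are already recorded, so no new data are needed. The Results section says that analysis was still under way, so the change could still be made at that stage.
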